**Methods/design::**

In this study, we will use our own front-to-back clinical research method. We plan to include 120 young and middle-aged female patients who meet the diagnostic criteria for HS. The untreated HS of the enrolled patients will be used as blank controls. The intervention group will be given acupuncture treatment. The assessment of scar area, color, hardness, thickness, itching and pain will be recorded for 30 days of treatment.

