#### Inclusion criteria

2.2.2

This study will be conducted in China. Patients will be recruited from Plastic surgery departments of the Second Affiliated Hospital of Shaanxi University of Chinese Medicine. We will enroll participants based on the following inclusion criteria:

(1)It meets the diagnostic criteria for HS;(2)The scar area is less than or equal to 6 cm^2^.(3)Female patients of 16 ≤ age ≤ 40 years old;(4)The time for the formation of fatigue marks exceeds 3 months;(5)Those who have voluntarily signed the informed consent;

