### Interventions

2.3

The participants included in the observation will be self-controlled, and each patient randomly selected 3 different scar treatment areas at the same site as observation specimens.

Control group: Take the untreated pathological scars of the participants as blank control. This group will not give any intervention.

Intervention group: Before the treatment, we will carry out strict physical examination and dermatological examination on the patient, and make sure that the patient has no obvious contraindications, and then carry out acupuncture treatment.

(1)Patient position: Choose according to the patient's scar location (supine position, lateral position or sitting position, etc.).(2)Operation steps: first disinfect the scar area and perform acupuncture in a circular shape on the local scar area of the patient. Needle retention time is 30 min, and the needle is moved twice during the needle retention process. The number of acupuncture depends on the size of the scar area of the affected area, with a minimum of 4 and a maximum of 15, each needle is about 3 cm apart, and the needle insertion is 1 cm to 1.5 cm. At the end of the 30-minute needle retention time, hold the hand on the eye of the needle with a medical swab and proceed in sequence.(3)Course of treatment: once every two days, 30 days as a course of treatment. Observe the scars every 15 days of treatment (Fig. 2).

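### The needle number and spacing do not fit the 6 cm² scar limit for compact scars, and the untreated control has no stated location relative to the needled field

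*Protocol article*

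**What the plan says.** **Eligibility (section 2.2.2).** The size criterion reads "The scar area is less than or equal to 6 cm", with the unit squared, so 6 cm². It does not say whether this applies to each scar or to the patient's total.

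**Needling (section 2.3).** The operator is to "perform acupuncture in a circular shape on the local scar area of the patient". The count is tied to scar size: "The number of acupuncture depends on the size of the scar area of the affected area". The permitted range and the gap between neighbouring needles are given in the same sentence: "with a minimum of 4 and a maximum of 15, each needle is about 3 cm apart".

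**Observed areas (section 2.3).** Participants are described as self-controlled, and "each patient randomly selected 3 different scar treatment areas at the same site as observation specimens".

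**Control (section 2.3 and abstract).** Section 2.3 says: "Take the untreated pathological scars of the participants as blank control". The abstract says: "The untreated HS of the enrolled patients will be used as blank controls". Neither gives a position or a distance from the needled scar.

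**Other statements on the comparison.** The abstract and introduction call the design a before-after one. Section 2.5 plans 60 patients per group, and section 2.6 has an envelope opened for each qualified case to determine the group.

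**Outcome (section 2.4.1).** Six items are scored 0 to 3: colour, height, hardness, itching, pain and tightness.

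**The concern.** The figures that define the intervention should be executable in the patients the trial admits. Here the scar limit is small and the needle pattern is large. If they cannot be met together, each operator will have to drop one of them (the count, the spacing or the layout), and the treatment delivered will vary in a way the protocol does not describe.

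The size of the pattern also matters for the comparison. A self-control is informative only if the control tissue is outside the treated field. When the smallest permitted ring is larger than a compact eligible scar, no part of that scar can serve as an untreated area. Half of the itemised score consists of sensations reported by the patient, which are difficult to attribute to one of two neighbouring patches of skin.

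**Working it through.** **Inputs.** Maximum scar area A = 6 cm² (section 2.2.2). Needle number n = 4 to 15, spacing s of about 3 cm, circular layout (section 2.3). Six items of 0 to 3 points (section 2.4.1). The plan gives no ring size, so there is no figure of its own to reproduce.

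**1. Largest round scar.** Radius = √(A/π) = √(6/π) = 1.38 cm. Perimeter = 2π × 1.38 = 8.68 cm. Needles at 3 cm: 8.68/3 = 2.9, below the minimum of 4. A square scar of 2.45 × 2.45 cm has a perimeter of 9.80 cm: 9.80/3 = 3.3, also below 4. Smaller compact scars fit worse, because the minimum count stays at 4.

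**2. Smallest permitted ring (n = 4, s = 3 cm).**

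| Measure | Radius | Enclosed area | Ratio to 6 cm² |
|---|---|---|---|
| Square with needles at its corners, 3 × 3 | – | 9.0 cm² | 1.5 |
| Circle, 3 cm along the arc: R = ns/(2π) | 1.91 cm | 11.5 cm² | 1.9 |
| Circle, 3 cm in a straight line: R = s/(2 sin(π/n)) | 2.12 cm | 14.1 cm² | 2.4 |

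Both ring radii exceed the 1.38 cm radius of the largest round scar, so a centred ring surrounds the whole scar.

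**3. Largest permitted ring (n = 15, s = 3 cm).** Circumference along the arc = 15 × 3 = 45 cm. Radius is about 7.2 cm and area 161 cm² (arc) to 164 cm² (straight line), about 27 times the limit.

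**4. Does the word about rescue it?** The 4-needle ring shrinks to 6 cm² only when spacing falls to 8.68/4 = 2.17 cm (arc) or 2 × 1.38 × sin(45°) = 1.95 cm (straight line). At 2.5 cm it still encloses 8.0 to 9.8 cm².

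**5. Scar shape.** For 6 cm² rectangles, needles along the outline = 2(w + L)/3:

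| Scar (cm) | Perimeter | Needles at 3 cm |
|---|---|---|
| 2 × 3 | 10.0 cm | 3.3 |
| 1.5 × 4 | 11.0 cm | 3.7 |
| 1 × 6 | 14.0 cm | 4.7 |
| 0.5 × 12 | 25.0 cm | 8.3 |
| 0.27 × 22.2 | 45.0 cm | 15 |

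Elongated scars can therefore take 4 or more needles along their outline, but 15 needs a strip about 22 cm long and under 3 mm wide. A 6 cm² rectangle fits wholly inside the 4-needle ring up to about 3.4 × 1.8 cm (arc) or 4.0 × 1.5 cm (straight line).

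**6. Score.** Six items × 3 = 18 points. Itching, pain and tightness = 3 × 3 = 9, half of the listed points. Section 2.2.1 gives a total of 21, which the six items do not reach; the share here is of the 18 itemised points.

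**The case against.** A reader might infer that the control is contaminated. The documents do not say so. In section 2.3 the same-site phrase is attached to the three treatment areas; the control has its own sentence, with no location. It could be part of the needled scar, another scar of the same patient, the pre-treatment state (the before-after label) or other patients (60 per group, envelope per case). Only the first reading puts it inside the ring. This objection stands, and the point about the control is conditional.

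It can also be said that if the figures conflict, at least one is wrong, and the 3 cm spacing may be the faulty one; the larger ring would then disappear. That is fair. The documents cannot show which figure is at fault, so the arithmetic proves a conflict, not the size of the field actually needled.

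The needles might also stand in the skin around the scar. Four could then be placed, but a compact scar would lie wholly inside them, and the upper end of the range would still be far out of scale.

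Two further inferences are tempting: that the treated-untreated contrast would show at most half of the effect, and that it is biased towards zero. The first needs an adjacent control, an effect spread evenly over the items and identical symptom scores in both areas; none of this is in the protocol. The direction is open as well. The control receives nothing, so patients know which area was needled, and their ratings could favour it. Nor can each area be put at 2 cm², since the text does not say that 6 cm² is the total over three areas.

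**Conclusion.** For compact scars the numeric conflict holds. At the 6 cm² limit a round scar has room for 2.9 needles where at least 4 are required; the smallest ring encloses 1.5 to 2.4 times the largest eligible area; and the top of the needle range is practically unreachable in the eligible population. This does not depend on how spacing is measured, and moderate departures from 3 cm do not remove it. It does not extend to elongated scars at the lower end of the needle range.

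The consequence for the comparison rests on one condition. If the control is taken from the same compact scar and the needling follows the stated figures, the control is inside the needled field and is not untreated. The protocol leaves that reading open by combining self-control and same-site areas without locating the control. The difficulty of scoring itching, pain and tightness separately applies to any adjacent-area control, whatever the ring size; it is a judgement about measurement, not a figure in the documents. No size or direction of bias is claimed.

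**What to change.** 1. Reconcile sections 2.2.2 and 2.3 on needle number, spacing, layout and scar-size limit, and say whether 6 cm² is per scar or per patient. Which figure should change is for the investigators; no value is proposed here.
2. State which control applies: another scar, the pre-treatment state or a separate group of patients. Require any within-patient control to be a separate scar wholly outside the needled field.
3. If an adjacent-area contrast is kept, base it on colour, height and hardness (0 to 9 points), and report itching, pain and tightness at patient level.

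Section 2.9 says recruitment has not started, so items 1 and 3 cost mainly wording. Item 2 may cost more: patients with only one scar could not contribute to a separate-scar contrast, and choosing between a within-patient and a between-patient control changes the comparison and its analysis.

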**Figure 2 F2:**
[figure not shown]
SPIRIT figure for the schedule of enrollment, interventions, and assessments.

Research requirements:

(1)Aseptic operation to prevent infection.(2)Acupuncture is prohibited when the patient is fasting or fatigued; acupuncture is prohibited in cases of local skin ulcers, tumors, fresh wounds, etc.(3)Avoid greasy, spicy food, coffee, strong tea and other diets.(4)Women can’t acupuncture during lactation and pregnancy. People with allergies should use acupuncture with caution.

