#### Diagnostic criteria

2.2.1

We will refer to the diagnostic criteria for pathological scars in “*Plastic Surgery*”. We will refer to the “Beauty Surgery” published by the People's Medical Publishing House (Beijing, China). The specific standards are as follows:

(1)HS occurs in various parts of the human body and occurs 4 weeks after trauma.(2)The lesion is limited to the scope of the wound; the early color is bright red and hard; it often shows excessive keratinization, ulceration and contracture; the texture and bulge of the mature stage are beyond the original damage range, and the mature stage is from June to December.(3)Consciously itching and burning pain in different degrees.(4)Symptoms can disappear after several months to 1 to 2 years, and gradually become dark brown, tending to be stable.

In addition, we will refer to the *“Vancouver Scar Scale”* combined with accompanying symptoms to develop scoring criteria, and then grade the severity of HS. The scale has a total score of 21 points. A higher score indicates more severe scarring. Mild: Total points ≤7. Moderate: 7 <total points ≤15. Severe: Total points> 15.

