#### Exclusion criteria

2.2.3

Patients will be excluded if they meet the following criteria:

(1)People with allergies and allergies to experimental drugs;(2)Ages <16 or >40 years;(3)Patients with renal cancer, bladder tuberculosis, urinary stones;(4)Patients with other malignant tumors;(5)Patients with blood system diseases, coagulation dysfunction and autoimmune diseases;(6)Patients with severe cardiovascular disease, cerebrovascular disease, hematopoietic system disease, and neuropathy;

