#### Conditions for participants to suspend and withdraw from the clinical trial

2.2.4

Researchers participating in clinical trials should carefully record the reasons for the suspension of the trial and the relationship with the clinical trial. It is necessary to clearly record the unwillingness of the subjects to continue the clinical trials, put forward the reasons for withdrawing from the clinical trials, and record the evaluation indicators at the time of discontinuation in detail.

(1)Those who cannot adhere to treatment;(2)Allergic reactions or serious adverse reactions during the test, the test should be suspended:(3)Those who have not been treated strictly according to the plan;(4)People who withdrew from the study on their own.

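### Section 2.3 bars needling in conditions that 2.2.3 does not exclude, and the check is described only for the intervention group, so a patient can qualify, be allocated to acupuncture and then be barred from it

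*Protocol article*

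**What the plan says.** The population is set in 2.2.2: "Female patients of 16 ≤ age ≤ 40 years old", who must also meet the diagnostic criteria. Those criteria, in 2.2.1, say of the lesion that "it often shows excessive keratinization, ulceration and contracture".

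The exclusion list in 2.2.3 has six items. It opens with "People with allergies and allergies to experimental drugs" and closes with "Patients with severe cardiovascular disease, cerebrovascular disease, hematopoietic system disease, and neuropathy". Pregnancy, lactation, skin ulcers and fresh wounds do not appear in it.

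The research requirements at the end of 2.3 say that "acupuncture is prohibited in cases of local skin ulcers, tumors, fresh wounds, etc", and that women cannot have "acupuncture during lactation and pregnancy. People with allergies should use acupuncture with caution".

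The examination that looks for contraindications is described in 2.3 under the intervention group, just before treatment. The control group in the same section receives nothing. Under 2.6 the allocation envelope is opened once a case has passed screening. The grounds for suspension or withdrawal in 2.2.4 include "Those who have not been treated strictly according to the plan".

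**The concern.** The eligibility rules and the treatment rules describe different populations. Every participant is a woman of an age at which pregnancy and lactation are realistic, and a feature that the protocol calls frequent in the qualifying scar is also a reason not to needle it. The bars are not part of the stated eligibility criteria, and the only described check belongs to the intervention group, so they take effect after allocation.

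At stake is comparability. If the groups consist of different patients, a bar to needling can remove a patient from the acupuncture arm but cannot touch a comparable patient in the untreated arm. Loss after allocation that depends on the arm can bias the comparison even when few patients are involved. Allergy is a separate inconsistency: an allergic patient is excluded under one section and treated with caution under another.

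**Working it through.** **Step 1. The rules side by side.**

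| Condition | Treatment rule (2.3) | Eligibility rule (2.2) |
|---|---|---|
| Pregnancy, lactation | Barred | Not an exclusion; all participants are women aged 16 to 40 |
| Local skin ulcer | Barred | Not an exclusion; ulceration called frequent in 2.2.1 |
| Fresh wound | Barred | Not an exclusion |
| Allergy | Caution only | Exclusion |

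The first three rows let in patients whom 2.3 forbids treating. The last row makes provision for patients who should not have been enrolled.

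**Step 2. One patient's path.** A lactating woman aged 30 with a qualifying scar meets 2.2.2 and none of the items in 2.2.3. She passes screening and the envelope is opened (2.6). If she is allocated to acupuncture, the pre-treatment examination in 2.3 should find the contraindication and she is not needled. She has then not been treated to plan, which can be read as a withdrawal ground in 2.2.4. If she is allocated to no treatment, no rule in 2.3 affects her and she is observed to day 60 (2.4).

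**Step 3. Dependence on the design.** The article supports two readings.

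- *Parallel groups* (60 per group in 2.5, envelopes in 2.6): the loss in step 2 occurs in one arm only.
- *Self-controlled* (Abstract; 2.3, with three scar areas per patient): a pregnant or lactating patient supplies neither condition, so the loss is balanced. A local ulcer could still remove only the needled area.

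**Step 4. Size: power.** Inputs from 2.5 are a difference of 11 points, alpha 0.05, power 95%, 49 per group, and 60 after a 20% increase. No SD is given, so 49 cannot be verified. Solving backwards from n = 2(z₁ + z₂)²SD²/Δ²:

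- Two-sided: SD = 11 × √(49/2) / (1.960 + 1.645) = 54.45 / 3.605 ≈ 15.1
- One-sided: SD = 54.45 / (1.645 + 1.645) ≈ 16.5
- Dropout step: 49 × 1.2 = 58.8, so 59; 49 / 0.8 = 61.25, so 62. The stated 60 lies between them.

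Assume SD 15 (which returns 49, two-sided) and 20% ordinary dropout in both arms, leaving 48 controls. Power = Φ(11 / (15 × √(1/48 + 1/n)) − 1.960), where n is the acupuncture arm after further loss from that arm only:

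| Extra loss, acupuncture arm | n | Power |
|---|---|---|
| 0% | 48 | 94.9% |
| 5% | 45.6 | 94.4% |
| 10% | 43.2 | 93.8% |
| 20% | 38.4 | 92.3% |
| 30% | 33.6 | 90.3% |

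This is an illustration only. The 11 points refer to the Constant–Murley questionnaire, which is not the outcome in 2.4.1.

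**Step 5. Size: bias, parallel reading.** If a share f of one arm is lost and those patients would have scored g points worse than the rest, the mean of the remaining patients is better than the full arm's mean by f × g. The six items in 2.4.1 score up to 3 each, a sum of 18. For assumed f of 5% to 20% and g of 2 to 6 points, the shift runs from 0.05 × 2 = 0.1 to 0.20 × 6 = 1.2 points. The documents supply neither f nor g.

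**The case against.** The mismatch in the text cannot be argued away, but several stronger conclusions that a reader might draw from it are not supported.

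- *That the loss must fall on one arm.* The article calls the trial self-controlled in the Abstract, Introduction, 2.3 and Discussion. One-sided loss follows only from the parallel-group reading of 2.5 and 2.6.
- *That barred patients leave the analysis.* Section 2.2.4 governs suspension and withdrawal and asks for the indicators at discontinuation to be recorded. It does not define the analysis population, which an analysis plan may do. That a patient left unneedled under the protocol's own rule counts as not treated to plan is also an inference, though a natural one.
- *That ulcerated scars are more severe, so the loss is informative.* No document says so, and ulceration is not one of the six scored items. The text of 2.2.1 sets it beside the early red, hard stage, and the Discussion links early itching to surface rupture. That makes a link plausible but does not establish it. Ulceration is also descriptive in 2.2.1 and not required for entry.
- *That an ulcer is a permanent bar.* The rule sits in the same item as fasting and fatigue, which are temporary, so it may mean only postponing a session. This reply does not reach pregnancy or lactation.
- *That the loss uses up much of the 60 − 49 = 11 spare patients per group.* That would need an assumed frequency, and the margin comes from a questionnaire that is not this trial's outcome.
- *That barred women would be needled.* The examination in 2.3 is there to prevent this.

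That last reply protects the patient but not the comparison. An examination made in one arm only, after allocation, is what would produce one-sided loss on the parallel reading.

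**Conclusion.** The contradiction between eligibility and treatment rules stands on either reading of the design. As written, the plan can allocate a woman to a treatment that it forbids her, and it gives allergy two different statuses. Both lists are printed in the article and they conflict, so this is not detail left to a fuller document.

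The bias is conditional. It requires parallel groups (or, with self-control, an ulcer on the needled area), loss of the barred patients' later scores, and a difference in outcome between those patients and the rest. The documents give no frequency for any of the conditions, so the bias cannot be computed; the 0.1 to 1.2 points above only show how it scales with assumed inputs. The effect on power is likely small: about one percentage point for a further 10% loss from one arm, with SD 15 assumed. The point should be corrected before recruitment, but it does not by itself undermine the trial.

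**What to change.** Reconcile 2.2.1, 2.2.3 and 2.3 so that eligibility and treatment rules describe the same patients. Which clinical rule is right is for the sponsor. Whatever it keeps, the plan should:

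1. check every retained bar to needling at screening, in every patient, before the envelope is opened;
2. give allergy one status in 2.2.3 and 2.3;
3. say whether the local ulcer and fresh-wound bar concerns a single session or the whole course;
4. keep a patient who becomes barred after allocation in her allocated group, and score her on days 15, 30, 45 and 60 as planned in 2.4.

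The cost is slightly fewer eligible patients and a procedural change: the examination in 2.3 moves earlier and covers all patients. Nothing in its description says that it establishes pregnancy or lactation, so screening must be able to detect whichever bars are kept. Section 2.9 says that recruitment has not started, so the text can be changed without affecting any enrolled patient.

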### Outcome measures

2.4

Complete the medical records of all patients 1 week before treatment. We will observe the indicators of each group of patients and record the case data on the 15th, 30th, 45th, and 60th day of treatment. All observation records were completed by the same person during the entire treatment period. Therefore, the observation records are all under natural light, room temperature 20 to 24 °C, to keep the room quiet.

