#### Primary outcome measures

2.4.1

We will use the international scar evaluation method: “*Vancouver Scar Evaluation Scale*” as the main standard for evaluating the efficacy.

(1)Color: 3 points for bright red, 2 points for light red, and disappear after pressing, 1 point for non-red or some gray, 0 points for normal skin color;(2)Height of scar marks: 3 points above 9 mm, 5 mm < 2 points for height ≤9 mm, 1 point for 1–5 mm, 0 points for flat or slightly depressed;(3)Hardness: 3 points for hard as cartilage, 2 points for hardness like rubber, 1 point for softness, normal for softness Skin score: 0 points;(4)Itching: 3 points for severe or persistent itching, 2 points for frequent and tolerable itching, sometimes 1 point for itching, and 0 points for no itching;(5)Pain: very intense 3 points for the “hyperalgesia”, 2 points for moderate-intensity allergic pain, sometimes 1 point for pain, and 0 points for no pain;(6)tightness: 3 points for strong tightness, not too tight Strong and tolerable score 2 points, slight tightness score, no tightness score 0 points. Efficacy index = (total score before treatment-total score after treatment) / total score before treatment × 100%.

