### Randomization and blinding

2.6

(1)The concealment of random schemes: After the scheme design is completed, the random schemes are enclosed in a sequence-encoded, sealed, light-tight envelope. Then it is handed over to the person in charge of the subject, after screening qualified cases, the envelope is opened to determine the grouping.(2)The recorder fills in the case report form with basic data and observation of the patient's local and systemic symptoms.(3)Unified production of various documents.(4)Check and confirm the correctness and completeness of all research data records and reports and case report forms, and ensure consistency with original data.

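### The section headed randomization and blinding masks no one, while one recorder scores a largely judged or self-reported primary scale against an untreated control

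*Protocol article*

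**What the plan says.** Section 2.4 (Outcome measures) assigns every rating to one individual: "All observation records were completed by the same person during the entire treatment period". It also fixes the light, the room temperature and quiet surroundings.

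Section 2.4.1 adopts a modified Vancouver scale "as the main standard for evaluating the efficacy". It has six items, each running from 0 to 3: color, height, hardness, itching, pain and tightness. Hardness is graded by feel, for example "3 points for hard as cartilage, 2 points for hardness like rubber". Height is graded in millimetre bands. The last three items are symptoms.

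Section 2.3 (Interventions) sets the comparator: "Take the untreated pathological scars of the participants as blank control", and then "This group will not give any intervention". No sham is described. The same section says "The participants included in the observation will be self-controlled".

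Section 2.6 is headed "Randomization and blinding". Its four items are sealed envelopes that are opened after screening, case report form completion ("The recorder fills in the case report form with basic data and observation of the patient's local and systemic symptoms"), uniform documents, and checking of records. None of them mentions masking of the recorder, the participant or the analyst.

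**The concern.** A heading that promises blinding over text that supplies none is more than detail left to a fuller protocol: the section is present and its content does not match its title. Sealed envelopes protect the assignment up to the moment they are opened. They do nothing for ratings made on days 15 to 60.

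The outcome is exposed to this. Against an untreated comparator, a woman knows which condition she, or her scar area, received, and her three symptom items carry that knowledge. The recorder's color and hardness grades are sensory judgments. With a single rater, any systematic lean enters every record and does not average out. The total then feeds the efficacy index in 2.4.1, and a ratio of the same form defines the response categories in 2.4.2. At stake is whether a positive result says anything about the scar itself, which the article says it wants to establish objectively.

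**Working it through.** **1. Composition of the primary score (section 2.4.1).**

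| Item | Range | Source of the grade |
|---|---|---|
| Color | 0–3 | observer, by eye |
| Height | 0–3 | observer, millimetre bands |
| Hardness | 0–3 | observer, by touch |
| Itching | 0–3 | patient |
| Pain | 0–3 | patient |
| Tightness | 0–3 | patient |

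The sum is 6 × 3 = 18, with 3 × 3 = 9 observer-rated and 9 patient-reported. (Section 2.2.1 gives 21 as the scale total; the six listed items sum to 18, which is used here.) Color and hardness make up 6 of the 9 observer points. Masking the recorder can protect the observer half at most.

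**2. What masks whom.** Under section 2.6, the recorder, the participant and the analyst are each not mentioned as masked. Under section 2.3, the participant cannot be masked, because nothing is given to the control. Under section 2.4, one person rates throughout, with no statement on masking.

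**3. Illustration of size.** The article gives no SD for the scar scale and no bias size. Its sample-size section uses a different questionnaire and states no SD either, so both inputs below are assumptions.

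- Per-item shift on the three observer-rated items: 0.1 to 0.3 point, so the total shift is 3 × 0.1 = 0.3 to 3 × 0.3 = 0.9 points.
- SD of the total: 2 to 5 points.
- n = 49 per group (section 2.5, before the dropout allowance), two-sided 5% test, true effect zero.

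With d = shift / SD and k = d × √(n/2), the false-positive rate is Φ(k − 1.96) + Φ(−k − 1.96).

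- Smallest case: d = 0.3/5 = 0.06; k = 0.06 × √24.5 = 0.297; rate 6.0%.
- Largest case: d = 0.9/2 = 0.45; k = 0.45 × √24.5 = 2.227; rate 60.5% (59.7% with the t distribution).

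| Total shift | SD 2 | SD 3 | SD 4 | SD 5 |
|---|---|---|---|---|
| 0.3 | 11.5% | 7.8% | 6.6% | 6.0% |
| 0.6 | 31.8% | 16.8% | 11.5% | 9.1% |
| 0.9 | 60.5% | 31.8% | 20.0% | 14.5% |

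Every cell exceeds 5%. At 60 per group the same two extremes are 6.3% and 69.3%; a larger trial only detects the bias more surely.

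**4. Within-patient reading.** If 120 women are their own controls and the two scores have an assumed correlation of 0.5, the standard error is √(2 × 0.5/120) SD = 0.0913 SD. A bias of 0.1, 0.2 or 0.3 SD then gives about 19.5%, 59% or 91%. The two-group range therefore does not carry over to that design.

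**The case against.** The strongest reply is that the article is silent rather than wrong. A reader might infer that the recorder knows the grouping. Nothing says so, and a full protocol could name a masked assessor. That stands as far as it goes: the supportable statement is that the section offers no masking under a heading that includes it, so nothing in the plan prevents the recorder from knowing.

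A reader might also infer from section 2.6 that the recorder and the person who opens the envelopes are different people, so that masking needs no change of duties. The text uses two labels but does not say that they are two people, nor that the recorder does not needle.

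Using a single rater is not itself a fault. It removes between-rater variation, and the fixed viewing conditions help consistency. Height, with its millimetre bands, depends least on judgment, so applying the same shift to it is generous to the illustration. It is also tempting to say that every bias must favor acupuncture. That is the most plausible direction against an untreated control, but the documents do not establish it.

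Finally, the design is unsettled. Sections 2.5 and 2.6 describe groups, whereas the abstract and section 2.3 describe a before-after or self-controlled comparison. This affects both the size of the problem and the form of the remedy, but not its existence.

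**Conclusion.** The concern holds in this form: the section that should describe blinding names no masked role, and the primary score combines sensory judgments by one recorder with symptoms from unmasked women, against no treatment. A difference on that score could come from observer bias, expectation or treatment, and the plan as written cannot tell them apart.

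The size is not known. The range of about 6% to 60% is an illustration that rests on assumed shifts and SDs, a two-group comparison with 49 per group, and no true effect. It models a lean in the observer-rated items only, and patient expectation would come on top. No single figure within the range should be read as the trial's error rate. The matter should be put right before recruitment, but masking the recorder cannot protect the symptom half of the score.

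**What to change.** 1. **Reconcile the design first.** State whether the comparison is between groups (sections 2.5 and 2.6) or self-controlled (abstract and section 2.3). In a pure before-after comparison there is no group to conceal, and masking to group has no meaning.
2. **Section 2.6.** State that the single recorder does not open envelopes, does not give acupuncture, and is not told the group or, if scars are compared within a patient, which scar area was treated. Color, height and hardness are scored before symptoms are asked about.
3. **Section 2.7.** Report the observer-rated subtotal (color, height, hardness; 0 to 9) with its confidence interval, separately from the patient-reported subtotal (itching, pain, tightness; 0 to 9), and state that the symptom items are unmasked. Base any claim of an effect on the scar itself on the masked subtotal's estimate and interval. Agreement in direction alone is too weak a test: with no effect it would occur about half the time.

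**Cost.** Wording and staff instruction, and no new data. If the present recorder also needles or opens envelopes, duties must be reassigned among existing staff. Needle marks may sometimes unmask the recorder, and the subtotal is less precise than the total. Section 2.9 says that recruitment has not begun and ethics review is still to come, so the change can be made now.
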